## Abstract

**Background:**

Depression is a major public health concern. Emerging research has shown that cognitive behavioral therapy for insomnia (CBT-I) is effective in treating individuals with comorbid insomnia and depression. Traditional face-to-face CBT-I encounters many obstacles related to feasibility, accessibility, and help-seeking stigma. CBT-I delivered via smartphone application could be a potential solution. This paper reports a protocol designed to evaluate the efficacy of a self-help smartphone-based CBT-I, using a waitlist group as control, for people with major depression and insomnia.

**Methods:**

A two-arm parallel randomized controlled trial is conducted in a target sample of 285 non-suicidal Hong Kong Chinese older than 17 years of age with major depression and insomnia. Participants complete an online rapid screening, followed by a telephone diagnostic interview. Those who meet the eligibility criteria are randomized in a ratio of 1:1 to receive either CBT-I immediately or to a waitlist control condition. The CBT-I consists of six weekly modules and is delivered through a smartphone application proACT-S. This smartphone app has been pilot tested and revamped to improve user experience. An online randomized algorithm is used to perform randomization to ensure allocation concealment. The primary outcomes are changes over the measurement points in sleep quality, insomnia severity, and depression severity. The secondary outcomes include changes over the measurement points in anxiety, subjective health, treatment expectancy, and acceptability of treatment. Assessments are administered at baseline, post-intervention, and 6-week follow-up. The recruitment is completed. Important adverse events, if any, are documented. Multilevel linear mixed model based on intention-to-treat principle will be conducted to examine the efficacy of the CBT-I intervention.

**Discussion:**

It is expected that proACT-S is an efficacious brief sleep-focused self-help treatment for people with major depression and insomnia. If proven efficacious, due to its self-help nature, proACT-S may be applicable as a community-based early intervention, thereby reducing the burden of the public healthcare system in Hong Kong.

**Trial registration:**

ClinicalTrials.gov NCT04228146. Retrospectively registered on 14 January 2020.

Major depressive disorder (MDD) poses a significant health problem. In Hong Kong, the 12-month prevalence rate of MDD among adults is estimated at 8.4% [1]. Sleep disturbance, in particular insomnia, is a frequent symptom of MDD. It has been estimated that as many as 90% of patients with depression have sleep quality-related complaints [2]. Furthermore, in addition to being a symptom, insomnia could contribute to MDD symptom maintenance and the development of subsequent major depressive episodes [3]. A review of 21 prospective studies found that insomnia was a predictor of depression and doubled the risk for depression [4]. One longitudinal study of 300 pairs of twins also found that sleep problems predicted depressive symptoms later in life [5]. In Hong Kong, it has been found that sleep disturbances predict suicide attempts among outpatient psychiatric patients [6].

There is strong evidence to support the efficacy and effectiveness of cognitive-behavioral therapy (CBT) in the treatment of both MDD [7] and insomnia [8, 9]. Given their high co-occurrence [10], it has been suggested that treatment for depression should be augmented with a sleep-focused intervention for patients with both symptoms. In fact, sleep treatments, such as cognitive-behavioral therapy for insomnia (CBT-I), have been found to attenuate non-sleep symptoms of MDD [11].

Despite its efficacy in tackling MDD, there exist multiple barriers that prevent patients from receiving CBT in many parts of the world, including Hong Kong. Traditionally, CBT for depression is offered through weekly in-person sessions, delivered by a professional therapist for 10–24 weeks. However, the over-stretched public healthcare system in Hong Kong cannot afford this frequency of care. The median waiting time for new routine cases ranges from 16 to 61 weeks [12], and the typical interval between sessions exceeds 2 to 3 months. Moreover, cultural barriers, especially stigma towards mental illnesses, are also hindering help-seeking behaviors in Hong Kong [13]. Many Chinese patients would see their illness as a source of shame, holding the belief that mental health problem is a result of inferior origins, failure of parents, or the sins of one’s ancestors [14]. Their illness could also cause unfavorable social evaluation and undermine help-seeking behaviors [15].

To overcome these structural and cultural barriers in the treatment of depression, self-help treatments, specifically smartphone-based programs, are proposed to be an economically viable and culturally acceptable mode to deliver empirically supported interventions. In contexts with scarce resources and strong stigma attached to mental illnesses, self-help treatments are feasible alternatives to professionally delivered treatments. With the increasing development and accessibility of technology, Internet and smartphone-based self-help treatments are becoming more readily available and increasingly popular. Emerging evidence suggests that patients with mild to moderate MDD are receptive and respond well to computerized CBT [16]. In a randomized controlled trial (RCT) examining Internet-based CBT for depression, 80% of participants reported satisfaction towards the treatment received, and 74% of participants felt the program was equal to or better than a “real” therapist [17]. Similarly, Internet-based self-help CBT-I was found to significantly reduce both insomnia and depression severity [18]. The effects of internet-based CBT-I on improving insomnia severity, sleep quality, and depression have been supported by multiple meta-analyses (e.g., [19–21]).

Not only are self-help treatments efficacious and effective, they are often preferred over traditional psychotherapy in places where mental health stigma remains prevalent. In a study conducted in Hong Kong examining the 12-month prevalence of major depressive episode [1], large proportions of patients considered self-help as their preferred treatment for depression, over general medical, mental health specialty, and traditional Chinese medicine. CBT-I, in particular, is more acceptable to this population as the treatment for sleep might be perceived as more “physiological” and less “psychological” than treatments for depression [22]. This is confirmed through the high receptiveness of Internet-based self-help CBT-I in a Hong Kong RCT [23]. With the high degree of smartphone penetration (85.8%) in Hong Kong [24], smartphone application might be another promising platform to provide self-help treatment there.

The unprecedented global pandemic of COVID-19 has highlighted the pressing need for remote delivery models of mental health services in the interest of public safety. There is emerging evidence to show that the pandemic and its aftermath have had detrimental effects on mental health [25], especially among people with pre-existing mental disorders and essential workers [26]. In addition, public healthcare systems worldwide face extreme pressure during the pandemic. Many non-urgent outpatient appointments are postponed, and psychiatric admissions are disrupted in response to COVID-19. The increasing need for remote assessments and therapist-client interactions may also accelerate the developments in eHealth/mHealth. Self-help app-based CBT could be utilized to fill the gaps in face-to-face care by increasing public’s access to much needed evidence-based mental health interventions. Therefore, community research that examines the feasibility and potential efficacy of self-help app-based CBT becomes even more relevant in the midst of the present pandemic and future public health crises. The present RCT offers one of the first evaluations of the use of a self-help smartphone app to deliver CBT-I in supporting people with MDD and insomnia in the community during the COVID-19 pandemic.

## Objectives

This paper describes the protocol for a two-arm parallel RCT study that compares the efficacy of a smartphone-based self-help CBT-I with a waitlist control group in treating people with MDD and insomnia in Hong Kong. It is hypothesized that, after the intervention, participants in the CBT-I condition will report a greater decrease in poor sleep quality, depression severity, and insomnia severity than those in the waitlist control condition. It is also hypothesized that the reduction in poor sleep quality, depression severity, and insomnia severity observed in the CBT-I condition will be maintained at 6-week follow-up. Furthermore, it is hypothesized that participants in the waitlist control condition will report a significant decrease in poor sleep quality, depression severity, and insomnia severity after receiving CBT-I.

## Methods

### Trial design

This is a two-arm, with equal randomization (1:1 allocation ratio) parallel, superiority RCT. It compares a self-help smartphone-based CBT-I intervention to a waitlist control condition. The self-help treatment is delivered through “proACT-S,” a smartphone application developed by the corresponding author’s research team. The results from a pilot study showed that proACT-S was efficacious for treating insomnia and was positively received by the users [23]. The current RCT is designed to test the efficacy of proACT-S in treating people with MDD and insomnia. Participants’ change in depressive and insomnia symptoms after the CBT-I intervention will be compared with that of the waitlist control group. The rationale for choosing waitlist control as the comparison condition is twofold: (1) it allows researchers to determine the effect of the intervention against not receiving treatment during the trial period and (2) it ensures that all participants will eventually receive the treatment.

Prior to trial entry, participants complete a two-stage screening. Their eligibility is assessed by an online survey, followed by a telephone diagnostic interview. After the two-stage screening, the assessments, randomization, and intervention are carried out via proACT-S. The research design is summarized in Fig. 1. The full SPIRIT checklist is provided as Additional file 1.

**Fig. 1 Fig1:**
[figure not shown]
The current RCT study design

### Study setting

This RCT is conducted in Hong Kong, where the 12-month prevalence of MDD among adults was estimated at 8.4% [1], and the weighted prevalence of insomnia among adults was 39.4% [25].

### Eligibility criteria

#### Inclusion criteria

To participate in this study, participants must fulfill the following inclusion criteria: (1) Hong Kong residents; (2) age ≥ 18 years; (3) sleep disturbance causes distress or impairment in social, occupational, and other important areas of functioning for at least three nights per week for at least 3 months; (4) Insomnia Severity Index [27] score ≥ 8; (5) Patient Health Questionnaire (PHQ-9 [28];) score ≥ 10; (6) being able to read Chinese and type Chinese or English; (7) have a smartphone device (iOS or Android operating system) with Internet access; (8) have a regular email address; (9) willing to give informed consent and comply with the trial protocol; (10) difficulty initiating sleep, maintaining sleep, or early morning awakening with inability to return to sleep at least once in the past 2 weeks; and (11) fulfilling International Statistical Classification of Diseases and Related Health Problems—Tenth Revision (ICD-10) diagnosis of depression (F32.00, F32.01, F32.10, F32.11, F32.2).

#### Exclusion criteria

Participants are excluded if they meet the following exclusion criteria: (1) Beck Depression Inventory-II (BDI-II) suicidal ideation score ≥ 2; or (2) receiving psychological treatment at least once per month; or (3) former proACT-S pilot clinical trial participants; or (4) currently taking prescribed psychiatric drugs such as antidepressants, tranquilizers, and sleeping pills regularly; or (5) carrying a diagnosis of psychosis or schizophrenia; or (6) participating in any other academic studies or clinical trials related to insomnia and/or depression; or (7) having current suicidal plans or acts or have had suicidal plans or acts within the past 12 months.

#### Withdrawal criteria

Participants are withdrawn if, during the main study trial, they (1) have concurrent psychological treatment at least once per month; or (2) are taking prescribed psychiatric drugs such as antidepressants, tranquilizers, sleeping pills regularly; or (3) are being diagnosed with psychosis or schizophrenia; or (4) are participating in any other academic studies or clinical trials related to insomnia and/or depression; or (5) have suicidal ideations defined as scoring ≥ 2 on the BDI-II suicidal ideation item; or (6) have experienced serious diseases, significant life events, hospitalization, or fatalities; or (7) withdraw their consent; or (8) do not complete each assessment within 2 weeks, do not submit consent within 2 weeks after proACT-S personal account registration, or do not log into proACT-S within 2 weeks after random group assignment. In addition, participants in the waitlist control group who fail the cross-condition contamination check are withdrawn. Participants in the waitlist control group are withdrawn if (1) they have viewed part or all treatment module content as shown by people who are undergoing this study’s treatment or who have completed this study’s treatment, or who are very familiar with proACT-S (except the proACT-S project team), or (2) they have watched part or all of the treatment module videos included in proACT-S, or (3) they have completed part or all of the treatment module homework in proACT-S.

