**Assessments:**								
*Primary outcome measures*		CBT-I	WLC		CBT-I	WLC	CBT-I	WLC
Depression severity (CES-D)		X	X		X	X	X	X
Insomnia severity (ISI)		X	X		X	X	X	X
Sleep quality (PSQI)		X	X		X	X	X	X
*Secondary outcome measures*		CBT-I	WLC		CBT-I	WLC	CBT-I	WLC
Subjective health (SF-12 Version 1)		X	X		X	X	X	X
Anxiety (HADS-A)		X	X		X	X	X	X
Treatment expectancy (modified CEQ)		X	X		X			X
Treatment acceptability (modified PARS)		X	X		X			X
Demographics	X							
Clinical comorbidity	X							
*Post-screening eligibility assessments*		CBT-I	WLC		CBT-I	WLC	CBT-I	WLC
Withdrawal criteria					X	X	X	X
Cross-condition contamination check						X		X

*CES-D* Center for Epidemiologic Studies Depression Scale, *ISI* Insomnia Severity Index, *PSQI* Pittsburgh Sleep Quality Index, *HADS-A* Hospital Anxiety and Depression Scale—Anxiety subscale, *CEQ* Credibility/Expectancy Questionnaire, *PARS* Participant Acceptability/Usability Rating Scale

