### Data analysis plan

The principle of intention-to-treat analysis will be adopted, in which all randomized participants with missing observations, from lost to follow-up or incomplete outcome assessments, will be handled by multiple imputation [53]. Missing data is assumed to be 5%.

Chi-square tests and independent *t* tests will be conducted to examine if participants in the CBT-I and waitlist control conditions differ in terms of demographic characteristics, clinical comorbidity, and baseline outcome scores. Multilevel linear mixed model based on the intention-to-treat principle will be used to calculate between-condition mean differences in the primary outcome changes in sleep quality, insomnia, and depression severity from baseline to post-intervention assessments. Multilevel linear mixed model based on the intention-to-treat principle will also be used to analyze secondary outcomes of the baseline to post-intervention change in subjective health and anxiety between CBT-I and waitlist control conditions. Clustering effect, significant baseline differences in demographics, clinical characteristics, and outcome variables will be adjusted for. Pair-sample *t* tests based on the intention-to-treat principle will be used to analyze changes in primary outcomes, subjective health, and anxiety obtained at post-intervention and 6-week follow-up separately for each condition. All comparisons are planned with a 5% two-sided significance level. Bonferroni adjustment will be applied.

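### Post-randomisation withdrawal rules, some outcome-related and one set for the waitlist only, are not reconciled with the intention-to-treat analysis of all randomised participants

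*Protocol article*

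**What the plan says.** All references are to the protocol article.

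- **Withdrawal criteria, both arms, non-adherence.** Participants are withdrawn if they "do not complete each assessment within 2 weeks" or if they "do not log into proACT-S within 2 weeks after random group assignment".
- **Withdrawal criteria, both arms, clinical events.** Participants are withdrawn if they "have suicidal ideations defined as scoring" at least 2 on the BDI-II item, or if they "are taking prescribed psychiatric drugs such as antidepressants, tranquilizers, sleeping pills regularly". Psychological treatment at least monthly, hospitalisation, serious disease and significant life events also count.
- **Withdrawal criteria, waitlist only.** In addition, "participants in the waitlist control group who fail the cross-condition contamination check are withdrawn".
- **CBT-I intervention.** Reasons for discontinuing treatment are listed separately, so the Withdrawal criteria concern leaving the study and not merely stopping CBT-I.
- **Table 2.** The withdrawal and contamination checks stand under "Post-screening eligibility assessments". They are marked only at post-intervention (week 7) and 6-week follow-up (week 13), both after allocation.
- **Data analysis plan.** Intention-to-treat is adopted, and "all randomized participants with missing observations, from lost to follow-up or incomplete outcome assessments, will be handled by multiple imputation". Withdrawal by protocol rule is not among the reasons named.

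**The concern.** Intention-to-treat needs outcomes from everyone randomised, whatever happens later. The Withdrawal criteria instead re-judge eligibility after allocation. Several triggers are plausible consequences of worse depression or insomnia. One overlaps with a primary outcome: regular use of sleeping pills leads to withdrawal, while use of hypnotics is a component of the Pittsburgh Sleep Quality Index. The contamination rule makes withdrawal unequal between arms by design.

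If withdrawal ends follow-up, or if scores from the triggering visit are set aside, outcomes become missing for reasons tied to the outcome and to the arm. Standard multiple imputation assumes missing at random (MAR): given the observed data, those missing resemble those who stayed. Outcome-driven withdrawal makes that doubtful. At stake is whether the primary comparison is the randomised one that the Data analysis plan claims.

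**Working it through.** **1. The plan's own figures.** The article gives no withdrawal rate; the nearest figure is attrition in Sample size. With f = 0.2 (d = 2f = 0.40), two groups and 12 covariates, the noncentrality is N × f² = 199 × 0.04 = 7.96 on 1 and 199 − 2 − 12 = 185 degrees of freedom. Power at two-sided 0.05 is 0.801, so 199 reproduces. Then 199 / (1 − 0.30) = 284.3, rounded up to 285, which also reproduces. Attrition of 30% is 0.30 × 285 = 85.5, about 85 people. The 5% missing data assumed in the Data analysis plan is 0.05 × 285 = 14.25, about 14 people. The article does not say whether rule-based withdrawals are counted in either figure.

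**2. How each rule could affect the baseline to post-intervention comparison.**

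| Trigger | Relation to arm or outcome | Post-intervention score |
|---|---|---|
| No log-in within 2 weeks | Both arms; in CBT-I it means the app treatment was not taken up | Falls due after withdrawal; not collected if follow-up ends |
| Late assessment | Both arms; non-adherence | May exist, but late |
| Suicidal ideation item, psychiatric drugs, therapy, hospitalisation | Plausibly follow from worse outcome | Check is scheduled at the same visit, so the score may exist |
| Contamination | Waitlist only | Same visit, so the score may exist |

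A criterion first met at week 13 cannot affect a week 7 score already collected. It bears on the follow-up analyses. By week 13 the waitlist has received CBT-I (Participant timeline), yet Table 2 repeats the contamination check there. The rule sets no time limit on watching module videos or doing homework, so these passages also need reconciling.

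**3. Size, if scores are lost.** All inputs here are assumptions except d = 0.40, which matches the planned f = 0.2.

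- Post score: y = 0.5 × baseline + √(1 − 0.5²) × error − 0.40 × arm, in SD units, with 2,000,000 per arm.
- Withdrawal: the worst-scoring share of each arm on s = y + c × noise, with c = 1 (strong dependence on the outcome) or c = 3 (weak).
- Analysis: baseline-adjusted regression on those who remain. In large samples this equals MAR imputation from arm and baseline.

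| Withdrawn, waitlist / CBT-I | Strong | Weak |
|---|---|---|
| 15% / 15% | 0.40 | 0.40 |
| 15% / 5% | 0.31 | 0.36 |
| 5% / 15% | 0.49 | 0.44 |
| 30% / 10% | 0.23 | 0.33 |
| 10% / 30% | 0.57 | 0.47 |

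At 15% / 5% the error is (0.31 − 0.40) / 0.40 = −23% to (0.36 − 0.40) / 0.40 = −10%; reversed, it is +10% to +23%. Average withdrawal is (15 + 5) / 2 = 10% in those rows and (30 + 10) / 2 = 20% in the last two, both below the 30% attrition planned.

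**The case against.** The strongest reply is that no passage removes withdrawn participants from the analysis set. The Data analysis plan keeps all randomised participants through imputation. A reader might infer that the plan excludes them and so breaks intention-to-treat outright. The documents do not support that: the conflict is over follow-up and data use, and it is left open. This part of the objection stands.

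It also stands that scores at the post-intervention visit may exist for many withdrawn participants, and that nothing says they will be discarded. The log-in rule is worded for both arms, so it should not be read as arm-specific; only the contamination rule is. All assessments run in the app, so someone who never logs in would yield no score with or without the rule. Parts of the same criterion, on consent and the baseline assessment, come before randomisation and raise no intention-to-treat question.

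The simulated sizes rest on chosen rates. No trigger is defined on a primary outcome score, and the imputation model is not given; that detail may sit in the full protocol or the analysis plan, and its absence here is no fault.

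The objection does not remove the conflict in the text. Study withdrawal is stated apart from treatment discontinuation, it is framed as eligibility after allocation, it includes a waitlist-only rule, and it is absent from the reasons for missing data that the analysis names.

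**Conclusion.** The Withdrawal criteria, Table 2 and the Data analysis plan are not reconciled on whose outcomes are collected and used after a withdrawal criterion is met. That much rests on the text alone.

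Bias is a risk, not a demonstrated result. It requires that scores are lost, that the loss depends on the outcome beyond what baseline explains, and that it differs between arms. Under assumed rates of 15% and 5%, a true effect of 0.40 SD is estimated at 0.31 to 0.36 when the waitlist loses more and at 0.44 to 0.49 when CBT-I loses more. With equal rates and equal dependence on the outcome there is no bias. A reader might infer that the plan is biased in a known direction; the documents give no withdrawal rates by arm, so neither direction nor size can be stated.

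**What to change.** Reconcile the three passages by separating withdrawal from treatment, or a protocol deviation, from the end of data collection.

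- Keep in the intention-to-treat analysis every observed outcome score of randomised participants, including late scores and those from the visit at which a criterion was met.
- Where follow-up is still open, continue to request the questionnaires unless consent is withdrawn. Recruitment closed in September 2020, so this may reach few people; the first step remains possible because the article describes the analysis as still to come.
- Use the withdrawal list only to define a per-protocol sensitivity set.
- Report withdrawals by arm and reason.

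The clinical rules for stopping treatment are not changed by this.

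The cost is wording in the protocol and analysis plan, recovery of scores already held, and possibly some further reminders. The downside is that the intention-to-treat estimate then includes contaminated controls and non-starters and may be somewhat diluted. The per-protocol set shows how much the result depends on them.

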### Participant timeline

Individuals interested in participating are invited to complete a two-stage screening. In stage 1 online rapid screening, they complete an online survey to review their eligibility. Those who have passed the online rapid screening will receive a link within the Qualtrics platform to sign up for the stage 2 telephone diagnostic interview screening. These telephone interviews are conducted by project assistants, who have been trained and supervised on the administration of the modified Chinese version of the CIS-R [34].

Individuals who do not meet the stage 2 telephone diagnostic interview screening eligibility criteria will receive a list of references related to insomnia and depression produced by the Department of Health and the Social Welfare Department under the Government of the Hong Kong SAR. Information regarding crisis hotlines and integrated community centers for mental wellness are provided to those currently with suicidal plans or acts, or those who have had suicidal plans or acts within the past 12 months.

Individuals who have passed the two-stage screening are directed to download proACT-S either from App Store or Google Play. Eligible participants are guided to register for their own personal accounts to enter the main study trial. They then complete the baseline assessment via proACT-S. After that, they are randomly assigned in a 1:1 ratio either to CBT-I condition or waitlist control condition.

Participants in the CBT-I condition start the 6-week CBT-I immediately after randomization, complete the post-intervention assessment right after they finish the treatment, and complete the follow-up assessment 6 weeks after the post-intervention assessment. Participants in the waitlist control group wait for 6 weeks without the proACT-S intervention and then complete the post-intervention assessment 6 weeks after the baseline assessment. The waitlist control participants start CBT-I (equivalent to that of the CBT-I group) immediately after completing the post-intervention assessment, and they complete the follow-up assessment right after finishing the 6-week CBT-I.

Emails and WhatsApp reminders are sent to participants to increase their engagement and to enhance treatment compliance. Upon completion of the study, each eligible participant receive cash coupons of HKD $100 as a token of appreciation for their participation. The proposed flow of participants is displayed in Fig. 2.

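### The waitlist contamination check is scheduled again at week 13, after that arm has received CBT-I by design, and the rule has neither a time window nor an exemption for it

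*Protocol article*

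**What the plan says.** The Withdrawal criteria section states that "participants in the waitlist control group who fail the cross-condition contamination check are withdrawn". Three grounds follow. The first is having been shown module content by people in, or familiar with, the treatment. The second is that "they have watched part or all of the treatment module videos included in proACT-S". The third is that "they have completed part or all of the treatment module homework in proACT-S". None of them carries dates, and none exempts treatment delivered by the trial.

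In Table 2, the row labelled "Cross-condition contamination check" has two marks, both in the waitlist column: one at post-intervention (week 7) and one at 6-week follow-up (week 13).

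The Participant timeline section says: "The waitlist control participants start CBT-I (equivalent to that of the CBT-I group) immediately after completing the post-intervention assessment". It then says that "they complete the follow-up assessment right after finishing the 6-week CBT-I".

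The Objectives include the hypothesis that "participants in the waitlist control condition will report a significant decrease in poor sleep quality, depression severity, and insomnia severity after receiving CBT-I". The Data analysis plan addresses this with paired t tests on measurements "obtained at post-intervention and 6-week follow-up separately for each condition".

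**The concern.** At week 7 the check does what its name says: a waitlist participant who has already seen the modules has been exposed to the other arm's treatment. At week 13 the same wording describes adherence. A waitlist participant who followed the timeline has watched videos and done homework in the app, and so meets the second and third grounds. One who never opened the modules meets neither.

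Two things are at stake. The first is the waitlist arm's withdrawal count. Because the check applies to one arm only, literal use would inflate that arm's withdrawals and make attrition look unequal between arms, and the Possible harms section lists attrition among the things monitored. The second, depending on what withdrawal does to data, is the set of people behind the third hypothesis, which is the only hypothesis that concerns the waitlist arm after treatment.

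**Working it through.** **Position of the marks in Table 2.** Counting columns, the two contamination marks fall in post-intervention waitlist and follow-up waitlist. The general withdrawal row just above has four marks, which fill both arms' columns at those two visits. That confirms the alignment.

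**Sequence for the waitlist arm**

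| Time | What happens | What the second and third grounds capture |
|---|---|---|
| Randomisation to week 7 | Waiting, no app treatment | Contamination |
| Week 7 | Outcomes; contamination check | Works as intended |
| Weeks 7 to 13 | Six CBT-I modules delivered by the trial | Assigned treatment |
| Week 13 | Outcomes; contamination check repeated | Adherence |

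Table 2 also schedules treatment expectancy and acceptability for the waitlist arm at week 13. The plan therefore asks these participants to rate the app treatment at the visit where having used it is a ground for withdrawal.

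**Planned sample size, reproduced first.** Inputs from the Sample size section: f = 0.2, two-sided alpha 0.05, power 0.80, 12 covariates. With a noncentral F test, lambda = f² × N, df1 = 1 and df2 = N − groups − 12, the smallest N is 199, whether 2 or 4 groups are entered. Inflation for attrition: 199 / (1 − 0.30) = 284.3, rounded up to 285. Both planned figures reproduce. They concern baseline to post-intervention, so the week-13 mark does not enter them.

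**How many people the literal rule could reach**
- Waitlist arm at 1:1: 285 / 2 = 142.5, about 142.
- After the planned 30% attrition: 142.5 × 0.70 = 99.75, about 100.
- At the 18.4% control-group attrition that the protocol cites from a meta-analysis: 142.5 × 0.816 = 116.3, about 116.

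The documents give no figure for waitlist uptake of the modules, so uptake is an assumption here. Of about 100 participants still in the study:

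| Assumed uptake | Withdrawn at week 13 | Not withdrawn (non-users) |
|---|---|---|
| 100% | 100 | 0 |
| 90% | 90 | 10 |
| 75% | 75 | 25 |
| 50% | 50 | 50 |

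If these withdrawals also removed week-13 outcomes, the loss would far exceed the 5% missing data assumed in the Data analysis plan. That comparison holds only under the condition stated.

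**The case against.** The best defence is that nobody would apply the rule this way. The check is named for exposure across conditions, and CBT-I that the trial gives to the waitlist arm is not that. The timeline, the week-13 expectancy and acceptability ratings, the third hypothesis and the paired t tests all show that treated waitlist participants are meant to stay. The week-13 mark may look back to the waiting period, or may serve only the first ground, content shown by others. A fuller protocol exists and may say so.

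This is a fair account of the likely intent, but it does not remove the conflict. The article prints the rule, its consequence and its timing, and these disagree. The week-7 check already covers the waiting period, so a second mark with no stated purpose leaves staff and readers to guess.

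The defence does succeed against four stronger inferences that a reader might draw:
- **That the week-13 outcomes are lost.** This is the final visit. Nothing says that the check comes before the questionnaires or that failing it deletes answers already entered. The Data analysis plan keeps all randomised participants and imputes for loss to follow-up or unfinished assessments; a completed week-13 assessment is neither.
- **That the primary comparison is damaged.** It ends at post-intervention, before the week-13 mark.
- **That about 100 or 142 is an estimate.** It is a ceiling under literal enforcement. No uptake figure and no withdrawal on this ground is reported.
- **That the week-7 check should become a mere analysis flag.** This contradiction shows no fault in the week-7 check.

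**Conclusion.** The contradiction between the Withdrawal criteria, Table 2 and the Participant timeline is real and can be seen on the page. Read literally, the week-13 check withdraws every waitlist participant who used the assigned treatment and retains only non-users: at most about 142 randomised, or about 100 after planned attrition, with actual numbers depending on an uptake that is not stated.

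Literal application distorts the waitlist withdrawal counts whatever happens to the data. The further consequence, a post-to-follow-up test for the third hypothesis based on non-users plus imputed values, follows only if withdrawal also removes week-13 outcomes, and the documents leave that open. The baseline-to-post contrast and the 199/285 calculation stand. This is a wrong rule for one visit and not just missing detail. Its reach is limited to one within-arm analysis and the reporting of withdrawals.

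**What to change.** Reconcile the three places:
1. In the Withdrawal criteria, limit the contamination check to exposure between randomisation and the waitlist post-intervention assessment, and exempt CBT-I delivered by the trial.
2. In Table 2, either delete the week-13 waitlist mark or add a note that it only looks back to the waiting period.
3. Before analysis, search the withdrawal log for waitlist participants withdrawn at week 13 under the video or homework grounds. Retain their data in the intention-to-treat analysis, and report how the rule was applied.

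The cost is one clause, one table cell or footnote, and a log check. Recruitment is already complete, so the log check is the part that matters most now. The sample size and the primary analysis do not change.
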